# Ethical Considerations

(a) Risk/benefit assessment:

From the data available of the product, there are no major health risks to the participants. However, if investigators find any information that might be associated with the IP, it will be conveyed to all the participants.

(b) Ethics Committee review and communications:

Essential documents will be submitted to the Institutional / Independent Ethics Committee (IEC) for its review. No patient will be enrolled in the study unless the IEC approves the study.

Updates will be given to the IEC each month. Serious adverse events will be reported within 24 hours of their knowledge.

All the communication with the IEC will be filed separately. Quest clinical services will communicate with the IEC on behalf of the sponsor.

(c) Informed consent process:

Information about the IPs and about the trial, procedures of the trial and risks-benefits will be conveyed to the patient so that s/he can take an informed decision. Patient Information Sheet (PIS) and Informed Consent Form (ICF) will be given to patients for reading. Illiterate patients will be read out in presence of an Impartial Witness. All questions and doubts of the patients will be resolved. Only eligible patients, fulfilling inclusion-exclusion criteria and willing to participate will be enrolled only through informed consent process. Each enrolled patient will get a unique identification number. Study coordinator will help PI and/or co-PI in conducting this process. In view of the contagious nature of the disease, if EC allows, consenting will be done post COVID-19 negative result, and s/he will be conveyed orally by the investigator, of the study.

(d) Subject confidentiality; Ownership of data and Coding procedures: Name of the patient will not be mentioned in the case record form or in the reports. There will be a mention of Patient Identification Number (PID) and initials of the patient instead. Sheet linking this PID and name of the patient will be safely secured with the study coordinator. Only members of IEC, monitors, auditors, regulatory persons will have access to the data of the enrolled patients. In all such cases, confidentiality about the participant’s identity will be maintained.

In case such as managing adverse event, identity will be revealed only to the concerned.

Coding will be done by the study coordinator. Participants’ identity will be concealed by a number. Study coordinator will keep the file linking these numbers to names in a safe and secured place at the site. Un-blinding list of the IP will be with the sponsor, and will not be shared with the team involved in the site activities.

Data, Study Monitoring and Supervision:

Data of the participants will be filled in by the study coordinator. Co-PI and PI will have rights to correct the data whenever needed. All the procedures will be carried out by adhering to the Good Clinical Practices (GCP). Monitor will have access to the study documents. Sponsor of the study can make audit of the study with prior appointment with the PI and the study coordinator.

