# Study Design

Overview of the Study Design

- This is a randomized, 2-arm, parallel group, double-blind, 1:1 ratio, controlled, exploratory trial with a study period of 30 days from the of enrolment.
- A total of up-to 75 known COVID-19 positive (with positive RT-PCR) patients will be enrolled in the study.
- All the patients enrolled in the study will get the Investigational Product (IP-1 and IP-2), or 2 capsule of Placebo in similar sized and colored bottles, two times daily for the 1^st^ 15 days. From 16^th^ day onwards patients will get one capsule twice daily i.e. IP-2 or capsule placebo up to day 30.
- Patients will undergo laboratory investigations upon enrolment and on last visit. RTPCR for COVID will be done on day 5 (+ 1 day).
- Patients and doctors treating will not be knowing what the participating subject has received. Subjects will be given coded bottles, containing dose for 30 days.
- No medicine which his/her physician is giving will be stopped. No modifications shall be suggested in their diet and daily routine physical activities.
- Thus, patients enrolled in the study will get the IP / Placebo in addition to the standard of care which they were already receiving at the time of enrolment.
- Half of patients will be getting Cap. IP and half will be getting Cap. Placebo throughout the study duration of 1 month.

Study period for enrolled patients will be 30 days:

- Enrollment (day 0): After Informed Consent Process, Demographics and other information for CRF will be recorded. Investigations: COVID 19 RTPCR, Lymphocyte subset analysis (TH1, TH2, Th17, IL6, NK Cells and CD markers); Immunoglobulin IGG (Serum); Immunoglobulin IGM (Serum); Liver Function Test and Kidney Function Test will be done. Cap. bottle will be given to the patients with the dose lasting for 30 days.
- Day 3±1: COVID-19 RT PCR (quantitative) test will also be conducted on day 3 (±1) on 5 subjects of each group
- Follow-up 1: Day (5±1): COVID-19 RT PCR (quantitative) test will be conducted for all subjects on Day (5±1). CRF will be filled for knowing the overall status.
- Follow up 2 (15^th^ day+ 2 days): This follow up will be clinical/telephonic. CRF will be filled for knowing the overall status.

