# **Methods and Procedures**

Patients attending COVID treatment center (YCM Hospital, Pimpri, Pune, India) of the investigators will be screened for their participation in the study. Patients should be COVID-19 positive, diagnosed recently. No discretion for enrollment will be made based on gender, color, religion and cast. Information about the study will be shared with the patients and their eligibility will be checked during screening. Those fulfilling this requirement and who are willing to participate will be given informed consent document and patient information sheet for reading. Adequate time will be given for reading the same and the same will be explained verbally. All questions will be answered to the patients’ satisfaction. Patient will be considered as enrolled only after consenting procedure is done.

Patients will be counseled about administration of IP (dose, timing, method etc.). In case of SAE / other event which necessitates to break the blind, it will be broken. Appropriate treatment will be provided and the IP might be discontinued if investigator thinks this in the best health interest of the participant.

Follow-Up:

After enrollment (Day 0), there will be one clinical and the next two: either telephonic or clinical follow-ups: first follow-up visit at day 5 (+1 day), second follow-up visit at day 15 (+2 days) and third follow-up visit at day 30 (+2 days).

Patients will need to make sure, there is no gap in consuming the IP.

Patients can call the study coordinator anytime for the queries if any.

Unscheduled Visits:

Patients will continue to visit his/her physician at the site for medical care with prior appointments for routine and regular check-ups. Study coordinator will try and combine their study follow-up visit with their regular visit at the site. Patients should, as far as possible, visit the site in case of medical emergencies.

Study Design:

This is a two arm, double blind, randomized, controlled, prospective study to determine safety and efficacy of Cap. IP in COVID-19 positive patients.

After enrollment, they will get the IP / Placebo in addition to their regular treatment they might be receiving for their condition. (2 capsules twice a day for prior 15 days and 1 capsule twice a day from day 16)

A total of 60 patients (Can be extendable to 150) will be enrolled in the study in different groups. The reason behind this sample size that, we can apply paired t test with adequate power for an exploratory study.

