# Study Assessments:

Participants will have a minimum of two follow-ups. Clinical assessment will be done; vitals will be noted, questionnaire will be filled-in and blood will be collected for various parameters.

Study Conduct:

Patients screened, eligible and willing will be enrolled in the study and IP will be dispensed. During screening, inclusion-exclusion criteria will be applied. Those fulfilling the criteria will be given detailed information about the study. Of those who are willing to participate will be asked to sign the informed consent form. Study coordinator with the principal or co-principal investigator will participate in the consent process.

Day of consenting will be done on the day of screening. After signing the consent form, on enrollment day, physical examinations will be done; blood will be withdrawn for investigations, case record form will be filled and IP will be dispensed. A copy of duly signed informed consent form will be given to them.

Follow-up Visit 1 [5^th^ day (+ 1) of the day of enrollment]: Questions will be asked about adherence, missed doses if any and adverse events if any. NP swab will be collected for RT-PCR of COVID-19

Follow-up Visit 2 [15^th^ day (+ 2) of the day of enrollment]: All the procedures for this visit will be the same as that of Visit 1, except that swab will not be collected for RT PCR.

Follow-up Visit 3 [30^th^ day (+ 2) of the day of enrollment]: All the procedures for this visit will be the same as that of Visit 2, and in addition, blood will be drawn for various markers.

Discontinued Patients:

Patients will be withdrawn/dropped from the study if they violate the protocol e.g. by participating in other study, by not taking the IP, not coming to the hospital for follow-up etc. Patients developing any serious disease, patients wanting to withdraw will also be withdrawn from the study.

Patients who have not turned for clinical follow-up will be called telephonically up to three times after the window period is over. During consenting they will be asked if it is alright with them.

However, as it is a ‘intent-to-treat’ (ITT) study design, data collected of such patients, till they are dropped out/withdrawn from the study will be included in the analysis.

Patients will be insisted to visit during the window-period. Those who miss this will still be continued into the study. On case-to-case basis, protocol waivers will be granted by the co-PI and/or the PI.

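### If the ethics committee allows it, consent may wait for a negative COVID-19 result; this contradicts the consent-first rules elsewhere and can tie consent to viral clearance, which the primary outcome measures

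*Protocol*

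**What the plan says.** Item (c) of Ethical Considerations gives a general rule, that eligible patients "willing to participate will be enrolled only through informed consent process". It closes with an alternative: "In view of the contagious nature of the disease, if EC allows, consenting will be done post COVID-19 negative result". All that it adds for patients on this route is oral information from the investigator about the study.

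The rest of the protocol sets a different order:

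- **Study Design (population):** "A total of up-to 75 known COVID-19 positive (with positive RT-PCR) patients will be enrolled in the study".
- **Study Design (day 0):** "Enrollment (day 0): After Informed Consent Process, Demographics and other information for CRF will be recorded". The day-0 investigations, including RT-PCR, and the dispensing of the bottle are listed after this.
- **Methods and Procedures:** "Patient will be considered as enrolled only after consenting procedure is done".
- **Study Assessments, Study Conduct (day of consent):** "Day of consenting will be done on the day of screening".
- **Study Assessments, Study Conduct (order of procedures):** "After signing the consent form, on enrollment day, physical examinations will be done; blood will be withdrawn for investigations". Dispensing comes in the same sequence, after the signature.
- **Study Assessment Table:** the consent form is marked at screening and day 0 only.

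Three further provisions bear on the point. Exclusion criterion 3 allows at most 48 hours between meeting the inclusion criteria and enrolment. Inclusion criterion 4 also admits some patients whose SARS-CoV-2 result is still pending. The Primary Outcome, printed within the adverse-event reporting format, is decline in viral load at 5 days, and early recovery, in COVID-19-positive patients.

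**The concern.** The trial studies patients who carry the virus at entry and measures how far viral load has fallen by day 5. A consent step that waits for a negative result makes consent depend on the event being measured. The protocol does not say whether enrolment waits as well, or whether study procedures go ahead on oral information with consent following later.

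One way, patients consented by this route have nothing left to measure on viral load. The other way, patients are randomised, sampled and dosed before documented consent, and those slow to clear the virus may never reach it. Both the validity of the viral-load comparison and the protection of participants are at stake.

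**Working it through.** The main check is a comparison of sections; arithmetic serves only as illustration.

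**Step 1: can all the rules be met together?** Methods and Procedures makes consent a condition of enrolment. Ethical Considerations (c), where the ethics committee (EC) allows it, makes a negative result a condition of consent. Together these make a negative result a condition of enrolment. Study Design requires the opposite. The pending-result patients of inclusion criterion 4 do not resolve this, since a pending result is not a negative one.

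**Step 2: enrolment waits for consent.** The patient has just tested negative, so day 0 has no detectable virus and no decline can be observed by day 5. The wait must also fit the 48-hour limit in exclusion criterion 3, so anyone who takes longer than that to turn negative is excluded.

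**Step 3: study procedures go ahead while the patient is positive.** Day-0 sampling, randomisation and dispensing then precede documented consent, against Study Design, Methods and Procedures and Study Assessments. For this route the protocol describes oral information from the investigator. It describes no oral consent, witness or record at entry; the impartial witness in the same item is for illiterate patients. Consent now follows viral clearance, a post-randomisation event.

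**Step 4: which test would trigger consent?** Scheduled PCR tests are:

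- day 0, all patients;
- day 3 (±1), five patients per group;
- day 5, all patients;
- visit 2 (day 15): Study Assessments says no swab is taken;
- visit 3 (day 30): as visit 2, with blood added.

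A patient still positive at day 5 has no later scheduled test. A test done in routine care might serve, but the protocol does not say so.

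**Step 5: what happens to the data?** Study Assessments and Data Analysis keep the collected data of patients who drop out or are lost to follow-up. Neither mentions patients who never give consent.

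**Step 6: illustration of selection under step 3.** The protocol's only computed figure is its sample size, from 5% v 35%, two-sided alpha 0.05, power 80% and ratio 1:1. It reproduces, with mean proportion (0.05 + 0.35)/2 = 0.20:

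- Kelsey: (1.960 + 0.842)² × 2 × 0.20 × 0.80 / 0.30² = 27.9, so 28 per arm.
- Fleiss without continuity correction: 27 per arm.

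The consent point does not depend on these figures. The protocol does not name the outcome behind 5% and 35%. **Assume** it is PCR negativity by day 5. With 30 per arm, the patients who could consent by day 5 number 30 × 0.05 = 1.5 (control) and 30 × 0.35 = 10.5 (treated), which is 12 of 60 or 20%.

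**Assume further** that unconsented data are excluded and that patients not yet negative are retained with probability q. The observed rate in an arm with true rate p is p / [p + (1 − p)q]:

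| q | Control | Treated | Difference |
|---|---|---|---|
| 1 | 5.0% | 35.0% | 30 points |
| 0.75 | 6.6% | 41.8% | 35 points |
| 0.5 | 9.5% | 51.9% | 42 points |
| 0.25 | 17.4% | 68.3% | 51 points |
| 0 | 100% | 100% | 0 points |

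So partial exclusion inflates the difference in this example, and complete exclusion erases it.

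**The case against.** The rule is conditional. Without EC permission the default order applies and the problem does not arise. That stands, and it limits the point to the case where permission is given. Permission would authorise the timing, but it would not reconcile the sections or break the link between consent and clearance.

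The oral clause suggests a benign intention: explain the study at the bedside and obtain the paper signature once contact is safe. This is probably the more natural reading, since delaying enrolment until patients are negative clashes most with the rest of the protocol. But the text calls the later step consenting and provides for no recorded agreement at entry, so it does not secure what was perhaps intended.

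The intention-to-treat statements may be taken to protect the data. They cover drop-outs and patients lost to follow-up, and leave patients who never consent unaddressed.

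A reader might infer three stronger conclusions, none of which the protocol supports:

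- **That the primary endpoint is lost.** This needs the delayed-enrolment reading applied to every patient. The primary outcome also names early recovery, which is not tied to a PCR result.
- **That patients who stay positive will be dropped from the analysis.** No section says so. It is a possibility left open.
- **That a definite loss of power follows.** The protocol gives no viral-load effect size or standard deviation, and no proportion of patients consented this way, so any such figure would be invented.

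Nor is it established that patients will be dosed before consent: Study Assessments puts dispensing after the signature, and the protocol does not say which provision prevails.

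**Conclusion.** The contradiction is certain and rests on the text alone. Where the EC allows the deferred route, the protocol gives two incompatible orders for consent and entry, and no section resolves them. Each way of following the deferred rule has a cost: patients who cannot contribute to the viral-load outcome, or study procedures before documented consent with consent dependent on a post-randomisation event.

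Bias in the analysis is conditional: it arises if data from patients who never reach consent are excluded. Its size cannot be derived from the protocol. The 12-of-60 figure and the 35 to 51 point differences show direction and rough scale only, under the assumptions that 5% and 35% are day-5 negativity rates and that retention of non-negative patients is 0.75 to 0.25. The point should be settled before enrolment, because an analysis plan cannot repair consent that was never obtained.

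**What to change.** Delete the sentence from Ethical Considerations (c), or reconcile it with Study Design, Methods and Procedures, exclusion criterion 3, Study Assessments and the Study Assessment Table. Either way, the protocol should state that documented consent precedes any study sample, randomisation or dose, and that consent never depends on a PCR result. Contagion can be handled by a contact-free consent procedure acceptable to the EC, carried out at screening or day 0.

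If any deferred route is kept, the protocol must also say what happens to the data of randomised patients who never reach the consent step.

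The cost is a small procedural change and an EC notification. The sample size, visit schedule and outcome measurements are unaffected.

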# Investigational Product Management:

(a) Investigational product packaging:

Capsules will be dispensed in the coded and sealed containers, which will last for 30 days.

(b) Dosing required during the study:

Total weight of each capsule in both the arms will be the same.

Dose is: two capsules twice a day for 15 days and from 16^th^ day one capsule twice a day, preferably empty stomach. One of the two capsules given during 1^st^ 15 days contains herbs to increase appetite and to digest the undigested, improving metabolism*.*

Timings should be: IP-1: before both meals, and IP-2 after 30 minutes after both meals

(c) Method of packaging, labeling, and blinding of study substances:

IP / Placebo, will be given to the enrolled patients. Labeling of the pouches/bottles will have all the essentials required. Blinding and coding will be done by the sponsor.

(d) Method of assigning treatments to Subjects and the Subject identification code numbering system:

Alfa-numeric identification numbers will be assigned to the participants.

(e) Storage conditions for study substances:

IP will be securely stored in cupboards with lock and key; at room temperature. Access will only be with the investigators.

(f) Investigational product accountability:

Bottles of IPs in sufficient quantity for a period of 30 days for each participant. Receipt and dispensing book will be maintained for the IP.

Participants will be asked to return, partially completed or unopened bottles. Proper recording will be maintained for dispensing and retrieval of the IP.

(g)Policy and procedure for handling unused investigational products:

All the unused IP will be sent to the sponsor.

# Data Analysis

Overall blinding will be broken at 30 days i.e.at the end of the study. Depending upon ADRs / SAEs, individual blinding might be broken on case-to-case basis.

Paired t test and any other appropriate test will be applied for analysis.

As this is intent-to-treat design, all the data, even the dropped-out patients’ and lost to follow-up patient’s collected data will be analyzed.

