# Study Rationale

COVID -19 is a respiratory illness that has led to a pandemic, affecting more than 200 countries in the world. Due to sudden advent and rapid spread of infection, no antiviral drug has been found to be effective since its onset.

1. While there is no medicine for COVID-19 as of now, enhancing the body’s defense system (immunity) plays an important role in maintaining optimum health and the IP (study drug) might possibly play an important role in enhancing immunity.
2. Role of study drug as an antiviral could also be tested.

The proposed trial is to check efficacy of Cap. IP in the management of COVID-19.

We intend to enroll up-to 75 COVID positive patients in the study. Eligible and willing patients will either get Cap. IP as an add-on therapy to the SOC (Standard of Care) or placebo (inert substance) as an add-on therapy to the SOC.

Aim: To assess the efficacy and safety of Cap. IP in the management of COVID 19 patients and also in boosting innate immunity.

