**Sample size: Cross- sectional, Cohort and Randomized Clinical Trials**

| Two sided significance level ( 1 alpha) | 95 |
| --- | --- |
| Power ( 1-beta. % chance of detecting) | 80 |
| Ratio of sample size, Unexposed/ exposed | 1 |
| % of Unexposed with outcome | 5 |
| % of Exposed with outcome | 35 |
| Odds ratio | 10 |
| Risk/ Prevalence ratio | 7 |
| Risk/ Prevalence | 30 |

|  | Kelsey | Fleiss |
| --- | --- | --- |
| Sample Size Exposed | 28 | 27 |
| Sample Size Non exposed | 28 | 27 |
| **Total Sample Size** | **56** | **54** |

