- Efficacy of the herbal extracts in COVID 19 positive patients (in declining viral load: time-point: 5 days and early recovery)

Secondary Outcomes:

- - Efficacy of the herbal extracts as an immune-modulator - TH1, TH2, Th17, IL6, NK Cells and CD markers; Immunoglobulin IGG (Serum); Immunoglobulin IGM (Serum): at 30 days.
  - Efficacy of the investigational product in reducing sequela of the disease
  - Safety analysis (Liver Function Test and Kidney Function Test) including serious allergic reaction of: rash, itching/swelling, severe dizziness, trouble breathing.

1. Details about the Investigator*

Name

Address

Telephone number

Profession (specialty)

Date of reporting the event to Ethics Committee:

Signature of the Investigator

Information marked ‘*’ must be provided.

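### The only test the protocol names, a paired t test, measures change within an arm rather than IP against placebo, and it contradicts the protocol's own two-group sample-size calculation

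*Protocol*

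**What the plan says.** - **Analysis.** The protocol's Data Analysis section names one test: "Paired t test and any other appropriate test will be applied for analysis". No section names a between-arm test, model or effect measure.
- **Sample size, in the text.** Methods and Procedures, under Study Design: "The reason behind this sample size that, we can apply paired t test with adequate power for an exploratory study".
- **Sample size, in the table.** The table that follows is a different calculation. It compares two independent groups on a binary outcome, 5% in the unexposed and 35% in the exposed, with 80% power and a two-sided 5% level (printed as "Two sided significance level ( 1 alpha) | 95"). It gives 28 per group (Kelsey) or 27 (Fleiss).
- **Design.** The Study Design section describes a "randomized, 2-arm, parallel group, double-blind, 1:1 ratio, controlled, exploratory trial". The Study Rationale gives the comparator as "placebo (inert substance) as an add-on therapy to the SOC". The flow chart shows 30 patients in each arm.
- **Primary outcome.** The outcome list printed within the adverse-event reporting format gives efficacy "in declining viral load: time-point: 5 days and early recovery". It does not say whether this is binary or continuous.

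**The concern.** No matching of patients across arms is described. The only available pairs are day 0 and follow-up in the same patient: RT-PCR at days 0 and 5, and immune markers at days 0 and 30. A paired t test on these asks whether an arm moved over time. Mild to moderate COVID-19 under standard of care can be expected to move in both arms without any drug effect.

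A significant paired test in the IP arm would therefore say little about the product. Finding significance on IP but not on placebo is not a comparison of the arms either. Randomisation, blinding and placebo protect the conclusion only if the arms are compared with each other.

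The protocol also gives two incompatible reasons for one sample size: a paired t test in the text, and a comparison of two proportions in the table.

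**Working it through.** **1. The plan's own figure.** Inputs from the sample-size table: p1 = 0.05, p2 = 0.35, two-sided alpha 0.05, power 80%, ratio 1. The mean proportion is 0.20, and (1.960 + 0.842)² = 7.849.

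- Kelsey: n = 7.849 × 2 × 0.20 × 0.80 / 0.30² = 27.9, so 28 per arm.
- Fleiss, no continuity correction: n = [1.960 × √(2 × 0.20 × 0.80) + 0.842 × √(0.05 × 0.95 + 0.35 × 0.65)]² / 0.30² = (1.109 + 0.441)² / 0.09 = 26.7, so 27 per arm.

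Both printed figures reproduce, but as a comparison of IP with placebo on a binary outcome. They give no support to a claim about a paired t test.

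**2. What 30 per arm can detect on a continuous scale.** Normal approximation, 80% power, in SDs of the change score:

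- Paired test within one arm: 2.802 / √30 = 0.51 SD.
- Comparison of change between arms: 2.802 × √(2/30) = 0.72 SD.

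Adequate power for the paired test is therefore not adequate power for the comparison the trial was randomised to make.

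**3. The paired test when the drug does nothing.** The protocol gives no mean change and no SD. The common improvement in both arms is therefore an assumption, expressed as d in SDs of the change score and shown over a range. With n = 30, the paired t statistic in each arm follows a noncentral t distribution with 29 degrees of freedom and noncentrality d√30; the two-sided critical value is 2.045. Let p be the rejection probability. The arms are independent, so the probability that IP shows a significant improvement while placebo is not significant is very nearly p(1 − p).

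| Common improvement d (SD) | IP-arm paired test significant | IP significant, placebo not |
| --- | --- | --- |
| 0.25 | 26% | 19% |
| 0.33 (one third) | 42% | 24% |
| 0.5 | 75% | 19% |
| 0.67 (two thirds) | 94% | 5.5% |
| 0.8 | 99% | 1% |

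The two columns must be read together by row. The right-hand column cannot exceed about 25%, the maximum of p(1 − p) at p = 0.5. It falls at large d because the placebo arm becomes significant too.

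**4. The between-arm comparison under the same conditions.** A two-sample t test on change, in 20,000 simulated trials with 30 per arm, rejected in 4.8%, 5.2% and 4.9% of trials at d = 0, 0.5 and 0.8.

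**The case against.** The strongest reply is that the sentence does not stop at the paired t test. Its catch-all clause allows a between-arm test, the paired test is nowhere called primary, and nothing says that change within an arm will be taken as efficacy. The sample-size table shows that a two-group comparison was in mind. A statistical analysis plan may exist, and the exact model, covariates and handling of the detection limit are commonly left to it. All of this stands.

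It limits the point in two ways. A reader might infer that natural recovery will be reported as efficacy. The documents do not support that: it follows only if the paired test is used as the efficacy test. A reader might also infer that the deciding test will be chosen after the data are seen. The protocol does not say so, and an analysis plan not shown here could fix the test in advance.

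The reply does not remove the defect. The protocol states, in two places, a method that does not fit its design, and one of those statements contradicts the table beside it. A suitable analysis plan would leave both sentences wrong. The exploratory label does not help either, because the stated aim is still to assess efficacy in a placebo-controlled trial.

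**Conclusion.** The point holds in this form: the only test the protocol names, and the stated reason for its size, is a before/after test within an arm. It fits neither the parallel-group placebo-controlled design nor the two-proportion calculation. The open clause permits a comparison of IP with placebo but does not commit to one.

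The size of the risk is conditional on the paired test serving as the efficacy test. With 30 per arm and no drug effect, the false-positive rate in the IP arm would then be 26% at a common improvement of 0.25 SD and 99% at 0.8 SD. Reading significance on IP but not on placebo as an effect would err in 1% to 24% of trials over the same range, against about 5% for a between-arm test. These figures assume normally distributed changes, equal SDs in the two arms and complete data; the improvement itself is assumed, since the protocol gives none.

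**What to change.** 1. In Data Analysis, state that the primary efficacy analysis compares IP with placebo as randomised and reports an effect estimate with a 95% CI.
2. Match its form to the primary outcome. If the outcome is binary, define it and compare two proportions, which agrees with the existing table. If it is continuous, compare day-5 viral load (log10 or Ct, to be stated) by ANCOVA on the day-0 value.
3. If the continuous form is chosen, restate the sample-size basis, because the 5% against 35% calculation would no longer apply. Also confirm that the day-0 RT-PCR is quantitative: the day-0 list in Study Design does not say so, and only the footnote to the Study Assessment Table does.
4. Define the early-recovery part of the primary outcome and compare it between arms. Compare the day-30 immune markers between arms as well.
5. Label within-arm paired changes as descriptive only.
6. In Methods and Procedures, replace the paired-t rationale with the sample-size calculation that is actually used.

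For a binary outcome the cost is protocol wording and an outcome definition. For a continuous outcome it also needs a new sample-size calculation with an assumed difference and SD. Neither adds a visit; baseline and follow-up measurements are already scheduled, subject to the day-0 RT-PCR check in item 3.

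### For the viral-load primary outcome the protocol names only a paired t test; it fixes neither a measurement scale nor a comparison between the randomised arms

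*Protocol*

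**What the plan says.** The Primary Outcome entry (Protocol, placed after the adverse-event reporting format in the Study Treatment section) defines efficacy as "in declining viral load: time-point: 5 days and early recovery". Study Design and the Study Assessment Table provide for quantitative RT-PCR in all patients at day 0 and about day 5. Neither gives the reporting unit: copies, log10 copies or cycle threshold (Ct).

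The Data Analysis section gives the method in one sentence: "Paired t test and any other appropriate test will be applied for analysis". Methods and Procedures also ties the number of patients to that test: "The reason behind this sample size that, we can apply paired t test with adequate power for an exploratory study". The sample-size table that follows is a different calculation, a comparison of two proportions (5% vs 35%) for an outcome it does not name. The flow chart shows 30 patients per arm.

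**The concern.** Two things are left unsettled for the viral-load part of the primary outcome.

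- **The comparison.** The trial is randomised and placebo-controlled, but the one named test uses each patient as their own control. It asks whether load changed between day 0 and day 5. In an acute infection load is expected to fall in both arms, so a significant paired result in the active arm says nothing about the product.
- **The scale.** Viral quantity spans orders of magnitude. If the decline is taken as raw day 0 minus raw day 5, a tenfold better response barely changes the number analysed, and the mean is driven by the few patients with the highest baseline loads.

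At stake is whether a real effect on this outcome can be seen, and whether a positive result could be attributed to treatment.

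**Working it through.** **1. The protocol's own figure.** Inputs from the sample-size table: 5% vs 35%, two-sided 5% level, 80% power, ratio 1.

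- Kelsey: n = 2(1.960 + 0.842)² × 0.20 × 0.80 / 0.30² = 27.9, so 28 per arm.
- Fleiss without continuity correction: n = [1.960√(2 × 0.20 × 0.80) + 0.842√(0.05 × 0.95 + 0.35 × 0.65)]² / 0.30² = 26.7, so 27 per arm.

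Both match the table. They concern proportions, so they give no power for any t test on viral load. The statement that a paired t test has adequate power has no mean change or SD behind it.

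**2. What a raw difference measures.** The fraction of baseline removed by a fall of k log10 is 1 − 10^(−k):

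| Fall (log10) | Baseline removed |
|---|---|
| 1 | 90% |
| 2 | 99% |
| 3 | 99.9% |
| 4 | 99.99% |

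Between a 2-log and a 3-log fall the raw decline changes by less than 1% of baseline. The spread of the decline is almost entirely the spread of baseline.

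**3. Power by simulation.** The protocol gives no viral-load mean, SD or effect, so these inputs are assumptions: normal log10 baseline with mean 6, 30 per arm, two-sided 5% level, and an extra fall of 1 log10 on the product. Simulation error is about 1 percentage point or less.

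Falls of 2 vs 3 log10, SD of the fall 1.2:

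| Baseline SD (log10) | Between-arm t, raw fall | Between-arm t, log10 fall |
|---|---|---|
| 0.8 | 2.9% | 89% |
| 1.0 | 2.0% | 89% |
| 1.5 | 0.8% | 89% |
| 2.0 | 0.4% | 88% |

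Check of the log10 column: 1 / (1.2 × √(2/30)) = 3.23, and the non-central t distribution with 58 degrees of freedom gives 89%.

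Falls of 0.3 vs 1.3 log10, SD of the fall 1.0:

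| Baseline SD (log10) | Between-arm t, raw fall | Between-arm t, log10 fall |
|---|---|---|
| 0.5 | about 25% | 97% |
| 1.0 | about 10% | 97% |
| 1.5 | about 4% | 97% |
| 2.0 | about 1% | 97% |

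A case chosen to favour the raw scale (falls of 0 vs 1 log10, SD of the fall 0.5, baseline SD 0.5) gives about 81% on raw copies and nearly 100% on log10. At baseline SD 1.0 the raw figure drops to about 30%.

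**4. The test actually named.** With no treatment effect, a 2-log fall in both arms, baseline SD 1 and SD of the fall 1.0, the within-arm paired test rejects in about 50% of trials on raw copies and about 100% on log10. Under the same conditions the between-arm t test on log10 rejects in about 5%. A log scale alone therefore does not repair the paired test.

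**The case against.** **The raw scale is not in the document.** A reader might infer that the trial will analyse raw copies and so has almost no power. The text does not support that. It gives no unit, Ct is already logarithmic, the sentence allows another appropriate test, and transformation is commonly left to a statistical analysis plan, which is not shown. This stands, and the power loss has to be stated as conditional.

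**The lowest power figures are for a between-arm test that the protocol does not name.** This also stands. For the paired test on raw copies, with SD of the fall 1.2, power is 58%, 42%, 16% and 7% in an arm falling 2 log10 (baseline SD 0.8, 1.0, 1.5 and 2.0). In an arm falling 3 log10 it is about 77%, 56%, 23% and 10%. Those figures vary widely and are not uniformly low. But the paired test answers the wrong question, so its power is no defence.

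**The log10 comparator is idealised.** It assumes every result is quantifiable. With an assumed detection limit of 10² copies, about 24–34% of the product arm falls below it in the 2 vs 3 log10 case, and log10 power is about 67–86%. With a limit of 10³ it is about 47–74%. The raw test stays at 3% or less in both cases. So the ranking is unchanged, but a rule for undetectable results is needed.

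**Other markers.** A reader might extend the argument to IL-6 and the immunoglobulins. The mechanism needs multi-log falls, and nothing in the protocol indicates these for serum markers at day 30. That extension is not made here.

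What the open clause cannot do is excuse the choice that was made. The protocol names one test, rests its sample size on it, and that test does not compare the arms.

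**Conclusion.** The point holds in a limited form. The only named test does not compare the randomised arms on viral load, and the scale of the outcome is not stated. This is more than missing detail, because a better analysis is available from measurements the protocol already schedules.

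The size of the scale problem is conditional on raw copies being differenced and on the assumed inputs above. Between-arm power is then about 0.4–3% against 89% for falls of 2 vs 3 log10, and about 1–25% against 97% for falls of 0.3 vs 1.3 log10. Raw copies did worse than log10 in every case tried. Raw power was respectable only when both the falls and the SDs were small. If results are reported as Ct, this part does not arise, and only the missing between-arm comparison remains.

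**What to change.** - **Primary Outcome.** Define the viral-load component as log10 viral load at day 5, or as Ct for one named target on one assay. State the fixed value assigned to results below the detection limit.
- **Data Analysis.** For this outcome, replace the paired t test with a between-arm comparison of day-5 log10 load (or Ct), adjusted for the baseline value on the same scale. Report the ratio of geometric means (or the Ct difference) with a 95% confidence interval.
- **Methods and Procedures.** Remove or correct the statement that justifies the sample size by a paired t test, since the table beneath it is a two-proportion calculation.

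The cost is a few sentences, including the detection-limit rule, settled before the blind is broken. It needs no new data, visits or patients, because quantitative PCR at day 0 and day 5 is already scheduled for everyone.
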